# Introduction

Recent advances in genetic sequencing technology have made the process more affordable and quicker, making the technology more accessible for use in healthcare. Furthermore, online Direct-to-Consumer (DTC) genetic testing is becoming increasingly more popular and is marketed under the pretext of ‘recreational’ purposes. With interest and demand for genetic testing increasing, and as the field of precision medicine is steadily growing, the investigation of the psychosocial consequences of genetic testing is critical. Currently, genetic testing is routinely used for known single gene, autosomal dominant disorders such as Huntington’s disease. While procedures for testing for colorectal, breast and ovarian cancer susceptibility mutations has become common in clinical practice, few other cancers have similar processess. The primary objectives of predictive genetic testing for cancer susceptibility is to inform an individual of their increased risk, offer protective or risk-reducing interventions, and where available, appropriate surveillance. For specific cancers where environmental and/or behavioural factors affect risk e.g. lung cancer and skin cancers, testing has the potential to motivate people to change health behaviours to reduce their risk, or delay the onset of disease. A primary concern of genetic testing for cancer susceptibility is the possible negative psychosocial impact of reporting unfavourable results. Before implementing any predictive genetic testing protocols in healthcare, there is an obligation to ensure feasibility and that the benefits outweigh potential harms.

Melanoma is Australia’s 4^th^ most common cancer, with over 13,000 new cases diagnosed in 2016, and over 1,700 deaths annually (AIHW)^1^. Approximately 10% of primary melanoma patients have at least one (and usually only one) first degree relative with a previous melanoma diagnosis^2^. Familial melanoma is often described as having at least two first-degree (FDR) or second degree (SDR) relatives with a melanoma diagnosis. However in Australia, where incidence of sporadic melanoma are highest, familial melanoma is more often defined as having three or more relatives with melanoma or pancreatic cancer within one side of a family^3, 4^. Worldwide, it is estimated that 2-5% of melanoma cases would be attributed to a true inherited familial risk resulting from a high penetrance germline mutation^5, 6^. Between 20 to 40% of these familial melanoma cases are found to be associated with a *CDKN2A* mutation^4^. Further high penetrance genes that have been identified, including *CDK4, MITF, BAP1, TERT, POT1, ACD, TERF2IP, POLE* are rare, each associated with <1% of familial melanoma cases^7^. It is expected that a subset of familial melanoma cases would be attributed to multiple low penetrance risk variants (polygenic inheritance), and/or shared environment^5, 8^.

In Australia, the majority of genetic testing for familial melanoma has been conducted in a research setting. Presently, in most cases the inclusion of genetic testing does not impact clinical management, as someone with extensive personal history would be managed as ‘high risk’ regardless of identified germline mutation. Therefore, the clinical utility of genetic testing for familial melanoma has been questioned^9^. Others have highlighted the benefit of genetic testing for ensuring appropriate surveillance in as yet, unaffected family members^10^. Clinical research studies, however, have continued to show positive outcomes for predictive testing in familial melanoma. Clinical trials have reported that any negative psychological impact of genetic testing is short term^10^, and learning of a genetic susceptibility has provided motivation for greater sun protective behaviour and screening^11^. Furthermore, reporting of negative *CDKN2A* mutation status provides relief for members of *CDKN2A* families, and assists them in re-adjusting to appropriate prevention strategies if previously overly cautious^12^. Importantly, there has been no evidence to suggest that a negative result has instilled a false sense of security, with several studies showing sun protective behaviour and skin examinations did not decrease^10, 13^, and in some studies, actually increased after disclosure of negative mutation status^14, 15^.

Currently, it is recommended that pre and post genetic education and counselling accompanies test reporting, and is provided by a qualified genetic counsellor. However, considering clinical genetic testing is very likely to increase quickly in the near future, it is important to acknowledge logistical implications and consider alternatives for clinical implementation. Counselling and reporting of genetic test results for the *BRCA1*/2 gene by trained nurses or doctors has become routine practice in several oncology clinics in Australia and the UK^16, 17^. Feedback from patients and nurses has been positive and this model provides improved access to genetic testing^16^. Testing and reporting on the *CDKN2A* gene variant is a candidate for mainstreaming the procedure in dermatology clinics. The advantages that a genetic counsellor has in delivering genetic test results is their expertise in dealing with complex issues of inherited risk, unexpected or incidental findings and inconclusive results such as ‘variants of unknown significance’. The mode of inheritance and risk significance is well understood for *CDKN2A*. Furthermore, a positive CDKN2A result would not be unexpected as a strong personal and family history of melanoma is a prerequisite for testing. With appropriate training on providing genetic education and counselling, testing for *CDKN2A* could become a standard procedure for a dermatologist. In most cases, a dermatologist will already know their patient’s personal and family history and are in the best position to offer subsequent recommendations based on test results, such as skin examination intervals. The present study will include a pilot study to produce preliminary data to explore this concept.

Some aspects of reporting personal genetic results for familial melanoma remain to be investigated, or completely understood. Psychosocial aspects such as genetic fatalism or essentialism for this cohort has not been reported. Genetic fatalism or essentialism can be described as the belief that one has little control over health outcomes, and that personal future health is determined by their genetic code^18^. These beliefs are often associated with decreased motivation for protective health behaviour^19^. Furthermore, it is useful to identify psychological traits present in this cohort that are associated with the uptake of genetic testing, and any correlation with significant psychological impact or behaviour change. Additionally, it is unclear what impact genetic testing has in familial cases where a clear line of inherited risk is present, however no responsible mutation is identified, leaving the cause or level of personal risk unexplained. In the present study, the effect of genetic education, counselling and testing, and on genetic fatalism will be explored. Furthermore, the extent to which psychological and behavioural outcomes vary depending on whether there is an identified familial mutation will also be explored. Lastly, this study will evaluate whether the method of delivery (dermatologist compared with genetic counsellor) of genetic test results for familial melanoma influences (or is associated with) psychological and behavioural outcomes.

# **1.2 Aims**

Primary Aim: To understand and describe the participant’s experience with genetic education, counselling and testing, and living with familial melanoma through qualitative analysis of semi-structured interviews.

Secondary Aims: To identify psychosocial and behavioural impact of genetic testing in familial melanoma, using quantitative analysis of validated questionnaires guided by the Health Belief Model as a theoretical framework. This will be achieved by;

1. Evaluate psychosocial and behavioural impact of genetic education, counselling (and testing) in individuals with a familial melanoma, regardless of whether a causal mutation has been identified.
2. Explore genetic fatalism in a subset of participants and whether they feel that genetic counselling (+/- testing) affected their beliefs.
3. Determine whether the person conducting the counselling session (genetic counsellor/dermatologist) affects psychosocial and behavioural outcomes.
4. Evaluate what psychological traits are associated with uptake of testing, psychological impact and behavioural change.
5. Assessment of the clinician training protocol, and supporting documents, for providing genetic testing.

# **Study Design**

# **2.1 Methods**

This study will be completed in two stages with two separate cohorts.

Stage 1: Genetic testing and counselling, semi-structured interview, and questionnaires at multiple time points. (n=50)

Stage 2: A one-off questionnaire designed after analysis from stage 1. (n=200)

The cohort for stage 1 of the study will be made up of approximately 50 participants (depending on when data saturation is reached in qualitative analysis of interviews). These participants will all have a suspected inherited risk of melanoma, and will be further stratified into 3 groups for data analysis, including a) those with a positive CDKN2A mutation, b) those positive for a different mutation for melanoma risk, and c) those where no mutation is found. All groups will receive pre and post genetic education and counselling, questionnaires at multiple time points (see table 2), and will participate in a semi-structured phone interview to discuss their experience with genetic testing and counselling one month after receiving test results.

Interview data will be transcribed and evaluated qualitatively using thematic analysis. Questionnaires will compose of validated instruments (see table 1), and will be analysed as per each scale’s manual and standard procedures. Findings produced by questionnaire and interview analysis will then be used to design a novel questionnaire instrument for capturing psychosocial and behavioural impact of genetic testing has for familial melanoma.

Stage 2 of the study will validate the novel questionnaire instrument in a cross-sectional study, enrolling a second cohort of approximately 200 participants with suspected familial melanoma. This second stage of the study will provide a more complete dataset from which hypotheses and conclusions about the psychosocial and behavioural impact genetic testing has for familial melanoma. This information will be a valuable addition to the current literature and inform genetic testing practices in the future.

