Researchers at QIMR Berghofer have conducted a study into the genetics associated with melanoma risk. The QIMR Berghofer study does not include reporting genetic results back to their participants. However the research team would offer selected participants who are interested in genetic testing who meet the study testing criteria. The study coordinators at QIMR Berghofer will be supplied with a recruitment brochure to distribute. The brochure will provide contact details for our study team, and will instruct the reader to either call or email our team if they are interested in participating. Upon contact from a QIMR Berghofer study participant, we will then follow the above procedure used for previous UQ-DRC participants for recruitment.

Family members of enrolled participants, will be invited to join the study through the proband (individual who first enrolled). The proband will be asked at the baseline visit if they would like to invite any family members. During the proband’s baseline visit, a genetic counsellor will identify other family members that meet testing criteria, based on a pedigree of family history of cancer. We will provide participants with brochures to give out to interested family members. Upon contact from family members, the same procedure or recruitment will be followed, e.g. phone conversation, emailed PICF, follow-up call to answer questions and book in an appointment.

Doctor referrals for people who are high risk of melanoma, and are interested in participating in research are regularly received at the UQ-DRC. Therefore we would like to have an option of recruiting eligible individuals referred to our research group in this way. In these instances, the individual would be contacted by phone and given a description of the current study to gauge interest and determine eligibility. Thereafter the same procedure for recruiting previous study participants will be followed, as detailed above.

*2.2.2: Stage 2: Cross-sectional newly developed questionnaire*

Eligibility criteria: Individuals who are identified as having a strong personal and/or family history that would meet the criteria for genetic testing as per the GenoMELPREDICT tool^20^.

Individuals will be recruited from the following sources;

1. A registry of previous participants kept by University of Queensland’s Dermatology Research Centre (UQ-DRC), who did not participate in Stage 1 of this study.

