# **Dermatologist reporting genetic results**

Participants in Stage 1 of the study will be randomised to receive the genetic education, counselling and test reporting by either a genetic counsellor or a dermatologist (or dermatologically trained clinician). We will be using block randomisation, stratified by whether the participant is from a) CDKN2A positive family, or b) other familial melanoma mutation positive family, or c) no known melanoma mutation identified. Data linkage, descried in section five, will be used to identify the genetic status of past participants before randomisation to facilitate stratification.

The aim is to evaluate whether the person providing the genetic education and counselling (genetic counsellor or dermatologist), affects the psychosocial or behavioural outcomes. The dermatologists/clinician will be provided with training from genetic counsellors prior to providing genetic education, counselling and test reporting to participants. Questionnaire data collected throughout stage 1 of the study will be used to analyse any significant differences in psychosocial or behavioural outcomes.

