# **Data Analysis**

*7.1 Stage 1: Pre and post genetic counselling questionnaires*

All questionnaires used in Stage 1, are previously validated, with recommended protocols for quantitative analysis. In some cases, questionnaire responses will be pooled within previously defined groups (i.e. *CDKN2A* positive, other germline mutation positive, or no mutation found), and compared for significant statistical differences using paired t-tests or chi-square analysis. Differences between dermatologist and genetic counsellor reported results will also be analysed.

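### The 'no mutation found' group pools true negatives from known-mutation families with people whose family has no identified mutation, so the pooled questionnaire comparisons cannot give the family-level contrast the protocol promises

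*Protocol*

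**What the plan says.** Protocol 2.1 Methods divides the Stage 1 cohort of about 50 into three groups for analysis: CDKN2A positive, positive for another melanoma mutation, and "c) those where no mutation is found". The Stage 1 part of Data Analysis uses the same three, ending with "other germline mutation positive, or no mutation found", and says that in some cases questionnaire responses will be pooled within them and compared. Both definitions rest on the participant's own test result.

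Randomisation uses a different variable. Under Dermatologist reporting genetic results, allocation is "stratified by whether the participant is from a) CDKN2A positive family, or b) other familial melanoma mutation positive family", with a third stratum for no known mutation. Data linkage "will be used to identify the genetic status of past participants before randomisation to facilitate stratification".

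On who enters, 2.2 Recruitment says: "Family members of enrolled participants, will be invited to join the study through the proband". Eligibility can rest on family history as well as personal history.

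The Introduction separates two kinds of negative result. For the first, a negative CDKN2A "mutation status provides relief for members of" CDKN2A families. For the second, it calls the impact of testing unclear where inherited risk is evident but "no responsible mutation is identified, leaving the cause or level of personal risk unexplained". It then undertakes to explore how psychological and behavioural outcomes differ according to whether a mutation has been identified in the family.

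**The concern.** A participant from a CDKN2A-positive family who tests negative has been told that they do not carry the family's variant. A participant from a family with no identified mutation who tests negative has learned little about their own risk. The protocol's background expects relief in the first case and leaves the second as an open question, yet its grouping rule puts both in group c.

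If the two react differently, the group c mean describes neither. The promised contrast is between families with and without an identified mutation, and group c is not the second of these. Stage 1 questionnaire and interview findings also feed the design of the Stage 2 instrument (about 200 participants), so a blurred description of this group could carry forward.

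**Working it through.** **No plan figure to reproduce.** The Stage 1 size rests on qualitative saturation, and the protocol gives no expected size for any result group. The check therefore compares definitions and then illustrates size under assumptions.

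**Definitions side by side.**

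| Participant | Randomisation stratum (family) | Analysis group (own result) |
|---|---|---|
| Carrier, CDKN2A family | a | a |
| Negative, CDKN2A family | a | c |
| Negative, other-mutation family | b | c |
| Negative, no mutation known in family | c | c |

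The last three rows share one analysis group, and no section separates them. Reading group c as a family-level label does not help: true negatives would then move into a or b and be pooled with carriers.

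**Share of true negatives in group c.** None of these inputs is given in the protocol; all are assumed:
- k, share of the 50 from known-mutation families: 20%, 40%, 60%
- q, probability of carrying the variant in those families: 50%, 75%
- r, share of the other participants in whom a mutation is newly found: 0%, 20%, 40%

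True negatives T = 50 × k × (1 − q). Uninformative negatives U = 50 × (1 − k) × (1 − r). Share w = T / (T + U).

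**Effect on the group c mean.** Pooled mean = (1 − w) × (mean in U) + w × (mean in T), in SD units of change in distress. Three assumed pairs (U, T) are shown.

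| k, q, r | T | U | w | (+0.3, −0.5) | (+0.2, −0.4) | (0, −0.5) |
|---|---|---|---|---|---|---|
| 20%, 75%, 0% | 2.5 | 40 | 6% | +0.25 | +0.16 | −0.03 |
| 40%, 50%, 0% | 10 | 30 | 25% | +0.10 | +0.05 | −0.125 |
| 40%, 50%, 20% | 10 | 24 | 29% | +0.06 | +0.02 | −0.15 |
| 60%, 50%, 40% | 15 | 12 | 56% | −0.14 | −0.13 | −0.28 |

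The first and last rows are the extremes of the 18 combinations. For the first pair the two reactions cancel at w = 0.3 / 0.8 = 37.5%, and for the second at 0.2 / 0.6 = 33%. Four of the 18 combinations exceed 37.5%, all with k = 60%. In the third pair the uninformative negatives do not change at all, yet the pooled mean still shows a fall.

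**Precision after a split.** Take the third row and an approximate 95% half-width of 1.96 / √n SD for a mean. Pooled group c (n = 34): 1.96 / 5.83 = 0.34. Uninformative negatives alone (n = 24): 1.96 / 4.90 = 0.40. True negatives alone (n = 10): 1.96 / 3.16 = 0.62.

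**The case against.** **The randomisation strata differ from the analysis groups, which a reader might take as an error in itself.** It is not. Randomisation precedes testing, so family status is the natural stratifier, and the strata serve the counsellor versus dermatologist comparison. The two variables need not coincide, and the mismatch alone does not bias that comparison.

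**A reader might infer that group c is unreadable and is the study's main interest.** The documents support neither. The primary aim is qualitative and covers the whole cohort, the first secondary aim applies whether or not a causal mutation has been found, and families without an identified mutation are one of several gaps named in the Introduction. Pooling is planned only in some cases, and the thematic analysis works from individual transcripts. Family status is needed to assign a stratum, so the split should need little or no new data. An SAP that is not shown could also subdivide the group.

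**The size is uncertain.** The Introduction calls the impact in families with no identified mutation unclear, so opposite reactions are a possibility, not a documented fact. The Introduction also makes strong personal and family history a prerequisite for CDKN2A testing; affected relatives are more likely than not to carry the family variant, which pulls the share of true negatives down. At a quarter of group c, both opposite-sign pairs are diluted (to +0.10 and +0.05 SD), not cancelled.

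What stands after this is the grouping rule itself. It is written twice, it mixes two situations that the protocol distinguishes, and it does not answer the family-level question.

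**Conclusion.** The point holds for the pooled questionnaire comparisons. Group c, defined by individual result, mixes true negatives from known-mutation families with people whose family has no identified mutation, and so cannot give the contrast set out in the Introduction.

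Under the assumed ranges, true negatives are about 6% to 56% of group c. At the low end the group mean is only slightly diluted. Cancellation needs a share of roughly a third or more, and a reversed sign appears only towards the top of the range. These sizes rest wholly on an assumed mix and assumed reactions. A claim that a real contrast would vanish is not supported, because the protocol gives neither the mix nor the size or direction of the reactions. The point about definitions depends on none of these assumptions.

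**What to change.** In 2.1 Methods and in the Stage 1 part of Data Analysis, keep groups a (CDKN2A positive) and b (other mutation positive) as they are. There is no need to merge them. Split group c:

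- **c1:** negative for a variant known in the family.
- **c2:** no variant known in the family and none found in the participant.

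Use c2 for the question about families with no identified mutation, and do not pool c1 with c2. Class family status by what is known when the participant's result is reported, including a variant first found in a relative during the study. Record that status for every participant at that point, since data linkage covers only past participants. Report these small groups descriptively, with intervals.

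The family-based randomisation strata can stay.

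The cost is wording, one recorded item, and precision. In the example above, the half-width for the no-identified-mutation group rises from 0.34 SD (pooled) to 0.40 SD, and the true negatives alone have 0.62 SD. Groups of about 2.5 to 15 (c1) and 12 to 40 (c2) support estimation, not firm tests.

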# **2.2 Recruitment**

*2.2.1: Stage 1: Genetic counselling and education, questionnaires and phone interview*

Eligibility Criteria: Individuals who are identified as having a strong personal and/or family history of melanoma indicative of inherited risk, will be invited to join the study. The eligibility criteria is based on a recent publication by Taylor *et al* (2019), which describes a tool GenoMELPREDICT that can be used to predict *CDKN2A* mutational status in people from melanoma-prone families^20^. The criteria for a populations with moderate-to-high incidence of melanoma is 3 primary melanomas in an individual and/or families with ≥1 invasive melanoma and ≥2 other invasive melanoma and/or pancreatic cancer among first-degree or second-degree relatives on the same side of the family.

Individuals will be recruited from four sources;

1. A registry of previous participants kept by University of Queensland’s Dermatology Research Centre (UQ-DRC)
2. Selected QIMR Berghofer Medical Research Institute (QIMR Berghofer)’s  *Pathways from Genotype and Environment to MELANOMA*  study (ERM Project ID 25706 HREC/14/QPAH/495)
3. Family members of enrolled participants (with participants’ prior approval)
4. Referrals from local dermatologists or healthcare providers

Previous study participants of the UQ-DRC who are eligible for the study, will be contacted by phone and given a description of the current study to gauge interest in participation. A participant information and consent form (PICF) will be emailed out if there is interest in participating. Individuals will be encouraged to read through the document and discuss with family members and/or healthcare providers. Individuals will be recontacted 1-2 weeks after PICF has been sent out to discuss participation in the study, and to answer any questions individuals have. A time and date will be made for an appointment at the Clinical Research Facility at PA Hospital, at the participant’s convenience.

Researchers at QIMR Berghofer have conducted a study into the genetics associated with melanoma risk. The QIMR Berghofer study does not include reporting genetic results back to their participants. However the research team would offer selected participants who are interested in genetic testing who meet the study testing criteria. The study coordinators at QIMR Berghofer will be supplied with a recruitment brochure to distribute. The brochure will provide contact details for our study team, and will instruct the reader to either call or email our team if they are interested in participating. Upon contact from a QIMR Berghofer study participant, we will then follow the above procedure used for previous UQ-DRC participants for recruitment.

Family members of enrolled participants, will be invited to join the study through the proband (individual who first enrolled). The proband will be asked at the baseline visit if they would like to invite any family members. During the proband’s baseline visit, a genetic counsellor will identify other family members that meet testing criteria, based on a pedigree of family history of cancer. We will provide participants with brochures to give out to interested family members. Upon contact from family members, the same procedure or recruitment will be followed, e.g. phone conversation, emailed PICF, follow-up call to answer questions and book in an appointment.

Doctor referrals for people who are high risk of melanoma, and are interested in participating in research are regularly received at the UQ-DRC. Therefore we would like to have an option of recruiting eligible individuals referred to our research group in this way. In these instances, the individual would be contacted by phone and given a description of the current study to gauge interest and determine eligibility. Thereafter the same procedure for recruiting previous study participants will be followed, as detailed above.

*2.2.2: Stage 2: Cross-sectional newly developed questionnaire*

Eligibility criteria: Individuals who are identified as having a strong personal and/or family history that would meet the criteria for genetic testing as per the GenoMELPREDICT tool^20^.

Individuals will be recruited from the following sources;

1. A registry of previous participants kept by University of Queensland’s Dermatology Research Centre (UQ-DRC), who did not participate in Stage 1 of this study.
2. Registries kept by Australian research collaborators, of individuals who would fit the above inclusion criteria.

An email will be sent to eligible individuals, which will include a description of the study objectives and time involvement required to complete the questionnaire. The email will provide a web-link which will direct the individual to a website that incorporates the informed consent process and the questionnaire, to be completed online at the participant’s convenience.

*The questionnaire and the consenting process, and the research collaborators that will facilitate recruitment, and any other related documents for Stage 2, will be submitted to the HREC committee as an amendment after Stage 1 of the study is complete. This delay is necessary as the questionnaire development is based on outcome analysis of the first stage of the study.*

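### Stage 1 enrols relatives but compares mutation-result groups with tests that assume independent people, so the standard errors of these secondary comparisons tend to be too small

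*Protocol*

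**What the plan says.** **Recruitment (Protocol 2.2.1 and 2.3.1).** Relatives of enrolled participants are one of four Stage 1 sources: "Family members of enrolled participants, will be invited to join the study through the proband (individual who first enrolled"). The approach is an offer: "The proband will be asked at the baseline visit if they would like to invite any family members". Eligible relatives are identified from a pedigree and the participant passes on brochures. No maximum per family is given.

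**Sample and groups (2.1).** Stage 1 has "approximately 50 participants (depending on when data saturation is reached in qualitative analysis of interviews"). They "will be further stratified into 3 groups for data analysis, including a) those with a positive CDKN2A mutation", with two further groups: carriers of another melanoma mutation, and people in whom none is found.

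**Analysis (Data Analysis, 7.1).** In some cases responses are pooled within these groups and "compared for significant statistical differences using paired t-tests or chi-square analysis". Differences by provider are also analysed, with no method named.

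**Where family appears.** In the section on dermatologist reporting, randomisation is "stratified by whether the participant is from a) CDKN2A positive family", another mutation-positive family, or neither. That stratifies by the family's mutation status; it does not identify which participants are related. Data Management describes a coded ID per participant and mentions no family link. The protocol has no family cluster term, robust variance or one-per-family analysis.

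**The concern.** Relatives share genes, a family cancer history and often habits and beliefs. The Introduction itself attributes part of familial melanoma to polygenic inheritance "and/or shared environment". Their questionnaire scores may therefore be correlated.

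The grouping variable is itself inherited, so comparing result groups is largely a comparison between families. A test that counts each relative as a separate piece of evidence then gives too small a standard error, intervals that are too narrow and too many false positives.

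Whether outcomes differ by identified mutation is a question raised in the Introduction. Stage 1 findings also feed the Stage 2 questionnaire, and Table 1 lists many instruments at several time points, so the error would recur across many tests.

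**Working it through.** **No figure to reproduce.** The sample of about 50 rests on interview saturation, with no alpha, power, effect size or standard deviation behind it. The check therefore concerns only the effect of ignoring family.

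**Inputs**
- n: about 50 (Protocol 2.1).
- Participants per family, m: not stated; assumed mean 1.25 to 4.
- ICC of questionnaire scores: not stated; assumed 0.05 to 0.3.
- Alpha: the plan says only "compared for significant statistical differences"; assumed two-sided 5%.

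**Step 1. Formula, with each family wholly inside one group**

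Design effect DE = 1 + (m − 1) × ICC. True SE / nominal SE = √DE. Effective n = 50 / DE. Actual alpha = 2 × [1 − Φ(1.96 / √DE)].

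| m | ICC | DE | SE ratio | Effective n | Actual alpha |
|---|---|---|---|---|---|
| 1.25 | 0.3 | 1 + 0.25 × 0.3 = 1.075 | 1.037 | 46.5 | 0.059 |
| 2 | 0.1 | 1 + 1 × 0.1 = 1.10 | 1.049 | 45.5 | 0.062 |
| 3 | 0.2 | 1 + 2 × 0.2 = 1.40 | 1.183 | 35.7 | 0.098 |
| 4 | 0.3 | 1 + 3 × 0.3 = 1.90 | 1.378 | 26.3 | 0.155 |

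The formula treats families as equal in size. A mean of 1.25 gives 50 / 1.25 = 40 families. If 10 are pairs and 30 are single members, the size-weighted mean is (10 × 4 + 30 × 1) / 50 = 1.4. Then DE = 1 + 0.4 × 0.3 = 1.12 and √DE = 1.058. That is about 6% rather than under 4%, and still small.

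**Step 2. Simulation, allowing relatives to differ in result**

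Independent-samples t-test, two groups, N = 48, no true difference, 6,000 runs per cell. The simulation error of a 5% rate is √(0.05 × 0.95 / 6000) = 0.003. In the segregating case half the families carry a mutation, the proband is a carrier, each relative carries it with probability 50%, and non-carriers join the no-mutation group.

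| m | ICC | Whole family in one group: type I error (SE ratio) | Segregating: type I error (SE ratio) |
|---|---|---|---|
| 2 | 0.1 | 0.064 (1.06) | 0.060 (1.03) |
| 2 | 0.2 | 0.074 (1.11) | 0.057 (1.04) |
| 2 | 0.3 | 0.090 (1.14) | 0.067 (1.10) |
| 3 | 0.1 | 0.072 (1.11) | 0.058 (1.04) |
| 3 | 0.2 | 0.092 (1.18) | 0.074 (1.10) |
| 3 | 0.3 | 0.127 (1.30) | 0.073 (1.11) |
| 4 | 0.1 | 0.088 (1.16) | 0.060 (1.07) |
| 4 | 0.2 | 0.124 (1.29) | 0.076 (1.13) |
| 4 | 0.3 | 0.155 (1.40) | 0.095 (1.19) |

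The first scenario agrees with the formula. In the second the bias is smaller but keeps its direction.

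**Step 3. Two limiting cases**
- Every family carries a mutation and is split across groups: SE ratio 0.97 to 1.00, type I error 0.042 to 0.048. The bias vanishes or slightly reverses. The plan's no-mutation group makes this an unlikely description of the whole cohort.
- Provider comparison with individuals randomised: SE ratio 0.99 to 1.01, type I error 0.047 to 0.053.

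**Step 4. The paired test.** A paired t-test compares two measurements in the same person; it cannot compare separate result groups. The calculation therefore uses the unpaired test that such a comparison needs. If paired tests are used for change within a group, relatives' changes can still be correlated, but the relevant ICC is that of change scores.

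**The case against.** **The SAP is not shown, and 7.1 is brief.** No sentence says that relatives will be analysed as independent, and clustering is often left to the SAP. Part of this stands: an SAP could repair the matter. But the protocol does name its Stage 1 tests, and those tests make the assumption. Only for Stage 2 does it say that the plan will be developed further.

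**Few relatives may enrol.** Relatives are one source of four, the invitation is optional, and the relative must make contact. This stands, and is why the range must include the negligible case.

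**Relatives do not always share a result.** Groups are formed on the individual's own result, and the Introduction describes members of CDKN2A families who test negative. This stands. A reader might take the simple design effect as the answer and quote 12% (m = 3, ICC 0.3, DE 1.6), or 22% at m = 4 and ICC 0.5 (DE = 1 + 3 × 0.5 = 2.5, effective n = 50 / 2.5 = 20). Both need every family to lie wholly in one group, and nothing in the protocol supports an ICC of 0.5.

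**Change scores may be less correlated.** Stable traits shared by a family cancel in within-person change. This is fair for pre/post tests, but does not help a comparison of scores between groups.

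**The provider comparison.** A reader might infer that its standard error is wrong too, perhaps in the other direction. The protocol randomises participants and does not name the family as the unit; step 3 shows no material effect.

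**Exploratory status.** The primary aim is qualitative, and the mutation-group contrast is described as exploratory. This lowers the severity but does not make the standard errors right.

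**Conclusion.** The point holds for the mutation-group comparisons. With the named tests, their standard errors are too small when families contribute several members, scores are positively correlated within families, and the cohort includes families without a mutation.

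The size cannot be fixed from the protocol. Under an assumed two-sided 5% test it runs from negligible, through moderate inflation when carrier families segregate, to about 15% at the worst corner examined (4 per family, ICC 0.3, whole families in one group). Confidence is high on the mechanism and low on the size.

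A reader might infer that the study's main result is at risk and that the change is indispensable. The documents do not support that: the main result is a thematic analysis, these comparisons are secondary, and few relatives may join. Severity is moderate.

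**What to change.** - Record a family ID at enrolment. Pedigrees are already taken at baseline, so this is one extra variable.
- Report the number and size of families, overall and by mutation-result group, alongside the number of participants.
- Amend 7.1 so that the mutation-group comparisons take family as the cluster: a random intercept, or cluster-robust standard errors with a small-sample correction. Restrict paired t-tests to within-person change.
- Add a sensitivity analysis with one randomly chosen member per family. It also serves as the fallback if the clustered model cannot be estimated stably.
- No change to the provider comparison is needed on this ground while individuals are randomised.

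**Cost.** Confidence intervals become somewhat wider. With about 50 people, three groups and possibly many single-member families, the family variance may be poorly estimated and robust standard errors unstable. The one-per-family analysis also discards data.
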